### 11.2.5.3 *Interim analysis and early stopping rule for efficacy*

Formal interim analyses will be conducted at the discretion of the Data Safety and Monitoring Board (DSMB), or at any other time point recommended by the DSMB.

The interim analysis will be performed by an unblinded statistician, who will prepare a closed report for DSMB review and recommendations. Analyses will be presented with blinded codes for treatment arms to protect against the possibility that the DSMB report may fall into the wrong hands. The DSMB will have access to the allocation code and will discuss or report the results of the interim analysis with the Trial Management Group (TMG), e.g. in a joint meeting. The DSMB, together with the Chief and Principal Investigators, decide on the continuation of the study.

The Lan-DeMets spending function with Haybittle-Peto type boundaries will be employed as a guide for the DSMB. Under the Haybittle-Peto rule, the recruitment can be stopped during any of the interim analyses with a type I error probability of 0.001 for the primary endpoint while preserving the overall type I error rate for efficacy at the  $\alpha=0.05$  level at the final analysis.

Statistics will not be the sole basis for the decision to stop or continue, and the DSMB can advise to continue recruiting in the trial, or stop recruiting but continue to complete the intervention as per randomization in the remaining active participants, even if statistically the stopping boundary is crossed, e.g. in order to continue collecting more safety or immunological information or data for further sub-group analyses etc. The trial will not be stopped in case of futility unless the DSMB during the course of safety monitoring advises otherwise.

A detailed plan for interim analysis, the provisional stopping rules and how the stopping rules will be applied, will be drawn up prior to the start of the interim analysis and documented in the study statistical analysis plan.

In addition, the DSMB will review the quality of the trial data and the safety data at every scheduled meeting.

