#### 16.2.3.1 Operational

The DSMB meetings will be conducted via teleconference and consist of an open session, followed by a closed session. The open sessions can be attended by representatives of the investigators, including the Chief Investigators, Country Principal Investigators, and study statistician. Other investigators can also attend open session on an ad hoc basis. The funder can attend open DSMB sessions as observers. The Chair and at least one of the three other independent members together will constitute a quorum.

The DSMB will have a start-up meeting to discuss its mandate and discuss the protocol. If possible, a second meeting will take place shortly after the commencement of the study, e.g. when approximately 10% of participants have been recruited. After that, the frequency of the meetings will be determined by the Chair of the DSMB in consultation with the Chief Investigators. It is anticipated that the DSMB will generally meet twice per year during the life span of the study and have one meeting at the closure of the study.

During the first meeting, the DSMB members will review the timeline set out in the protocol for participant recruitment, informed consent documents and plans for data safety monitoring. Prior to subsequent meetings, open reports containing accrual and retention rates, participant characteristics, and serious adverse events will be sent to the DSMB members the week prior to any DSMB meeting. Only the DSMB members and the unblinded biostatistician will receive password-

protected closed reports of SARS-CoV-2 endpoints by randomisation arm. A full confidential report should be submitted in writing to the Chief Investigator at the end of each DSMB meeting

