#### **16.2.3.2 Role of the DSMB**

They are independent and look at the study overall and the nested malaria treatment trial from an ethical point of view of the participant safety, future participants, and society in general. It is their responsibility to prevent participants from being exposed to any excess risks by making a recommendation to the Investigators for the study or trial suspension or early termination if the safety or efficacy results are sufficiently convincing. For the nested trial component, the DSMB can choose whether to review the data blinded or to see unblinded data and analyses by study arm. A DSMB charter will be developed for this study that will supersede this section of the protocol. Any changes in the role of the DSMB relative to this protocol text will not be considered a protocol deviation and does require an amendment. Briefly, some of the suggested roles of the DSMB will include:

- To evaluate the progress of the study/trial in relation to the timeliness, data quality and other factors that can affect the overall objectives of the trial
- To ensure participant rights and safety are adhered to and that the protocol demands freely given informed consent
- To conduct any interim reviews if specified) when adequate data have been accrued of blinded or unblinded safety data and report back to the Chief Investigators with a recommendation whether the study or nested trial should continue, the protocol be modified, or the trial or trial arm be stopped.
- Review and any major deviations from the study protocol
- To review relevant information from other sources
- To review and approve modifications to the overall enrolment target based on the event rate.
- To inform the Chief Investigators and TMG of the need to make changes to the trial protocol
- To consider the blinded or unblinded interim data from the study and nested trial and relevant information from other sources.
- To determine how frequently any interim analysis of study or trial data should be undertaken.
- To consider any requests for unblinding and release of interim trial data and to recommend on the importance of this.
- To ensure that the study results are disseminated appropriately, and consideration be given to the implementation of the results into policy

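### Section 11.2.5.3 lets the DSMB report interim results to the Trial Management Group without limit and has investigators co-decide continuation, against the protocol's own closed-report rule

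*Protocol*

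**What the plan says.** Protocol section 11.2.5.3 starts with a conventional firewall. An unblinded statistician runs the interim analysis, "who will prepare a closed report for DSMB review and recommendations", and the arms are coded "to protect against the possibility that the DSMB report may fall into the wrong hands".

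The same paragraph then says that the DSMB, which can see the allocation code, "will discuss or report the results of the interim analysis with the Trial Management Group (TMG), e.g. in a joint meeting". It continues: "The DSMB, together with the Chief and Principal Investigators, decide on the continuation of the study".

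Appendix II describes a different arrangement:

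- **Section 16.2.3.1:** "Only the DSMB members and the unblinded biostatistician will receive" the password-"protected closed reports of SARS-CoV-2 endpoints by randomisation arm". Investigators are listed as attending open sessions. The section ends by sending the Chief Investigator a full written report after every DSMB meeting, without saying what it may contain.
- **Section 16.2.3.2:** the DSMB is to "report back to the Chief Investigators with a recommendation whether the study or nested trial should continue". Release of interim data is something the DSMB considers when asked.

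**The concern.** The Trial Management Group is made up of the people who run the study. Section 16.2.1.1 lists the Chief Investigators, the country Co-Principal Investigators, the study coordinators, the lead data manager and the lead administrators. Section 16.2.1.2 gives them day-to-day management.

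Under section 7.4, participants and follow-up staff know the assigned drug. What the team does not know is how SARS-CoV-2 clearance compares between arms, because the assays are done by blinded laboratory staff. Section 11.2.5.3, followed as written, allows that comparison to reach the team while the trial is still enrolling.

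A team that knows the trend could, without intending to, change whom it approaches, what co-medication is given, how hard it chases day-7 visits and swabs, and how it judges whether an adverse event is treatment-related. The last matters because treatment-related adverse events by day 7 are a secondary endpoint (section 4.3). Retention matters because the primary analysis is complete-case (section 11.2.6.2).

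**Working it through.** **1. The provisions side by side.**

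| Question | 11.2.5.3, start of the paragraph | 11.2.5.3, next sentences | Appendix II |
|---|---|---|---|
| Who sees interim results? | DSMB, in a closed report with coded arms | DSMB discusses or reports them with the TMG | By-arm SARS-CoV-2 results: DSMB and unblinded biostatistician only (16.2.3.1) |
| Is release the default? | No | Yes, no limit on content | No, considered on request (16.2.3.2) |
| Who decides on continuation? | DSMB reviews and recommends | DSMB together with the Chief and Principal Investigators | DSMB recommends to the investigators (16.2.3.2) |

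The middle column cannot be followed together with the other two.

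**2. Does another document settle it?** The charter clause in 16.2.3.2 says the charter will supersede that section of the protocol, meaning the DSMB appendix. It does not reach 11.2.5.3. What 11.2.5.3 leaves to the SAP is the interim plan and stopping rules, not who receives results.

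**3. The plan's own figure.** Section 11.1.3 gives 20% against 42.2% clearance, 134 completers (67 per arm), two-sided 0.05, 80% power. With pooled variance under the null:

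- mean rate = (0.20 + 0.422)/2 = 0.311; null SE = √(2 × 0.311 × 0.689/67) = 0.0800
- alternative SE = √((0.20 × 0.80 + 0.422 × 0.578)/67) = 0.0776
- z = (0.222 − 1.960 × 0.0800)/0.0776 = 0.84, so power is 80.0%. The figure reproduces.

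**4. How would a look usually end?** The same formula with the 0.001 boundary (critical value 3.29). The information fractions are assumptions, since timing is left to the DSMB.

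| Fraction | Per arm | Observed difference needed (20% control) | Chance of crossing at 20% vs 42.2% |
|---|---|---|---|
| 0.50 | 34 | about 39 points | 9% |
| 0.75 | 50 | about 32 points | 18% |

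Even if the planned effect is real, an interim look would mostly end in continuation. Any results passed to the TMG would then be known to it while it goes on running the trial.

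**5. A limit on the retention route.** The planned loss is 142 − 134 = 8, or 4 of 71 per arm. Take the most extreme pattern: every AL loss had cleared and every PA loss had not.

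- *No true effect, all 4 per arm lost this way:* 0.20 × 71 = 14.2 cleared per arm. AL becomes 10.2/67 = 15.2% and PA 14.2/67 = 21.2%, a spurious 6.0 points.
- *Planned effect, half-way look, 2 per arm lost afterwards:* the difference goes from 30/71 − 14/71 = 22.5 points to 30/69 − 12/69 = 26.1 points, a shift of 3.6.

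These limits hold only at 5% loss. They say nothing about the other routes.

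**The case against.** - **The section does not say that unblinded results go to the TMG.** This is correct. The analyses are presented with coded arms, the DSMB is the body given access to the code, and no sentence passes the code on. A reader might infer an instruction to unblind the investigators; the text does not support that. It is silent on what may be disclosed, and coded comparative results are still comparative results.
- **Appendix II is not a clean model of recommendation-only reporting.** This also stands. The report that 16.2.3.1 sends to the Chief Investigator has no stated limit, so aligning 11.2.5.3 with the appendix would leave a second route open.
- **There are real safeguards.** The primary endpoint is read by blinded laboratory staff, and allocation uses sequential sealed opaque packs from lists made by a UK statistician (section 7.3). Staff already know each participant's drug, so only the added effect of knowing the trend is at issue. These points limit the bias but do not resolve the contradiction.
- **The trial is exploratory, and interim analyses are an option meant to let promising findings be shared early (section 11.1.3).** That aim is met by release on a DSMB recommendation. It does not need default reporting to the TMG.
- **Investigators may properly take the final decision.** Agreed: section 16.2.3.2 implies it. The problem is a joint decision after the results have been discussed, not that the investigators decide.

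**Conclusion.** The contradiction is in the text and should be removed before any interim look, because disclosure cannot be reversed. Section 11.2.5.3 reports interim results to the TMG with no limit on content and makes continuation a joint decision. The opening of the same paragraph and Appendix II restrict the results and make the DSMB advisory.

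The size of the resulting bias cannot be computed. At the planned 5% day-7 loss, the extreme retention patterns above shift the difference by 3.6 to 6.0 points against a target of 22.2. Effects through recruitment, co-medication, swab completeness or adverse-event attribution are not bounded by that calculation.

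Two stronger readings are not supported:

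- **That the Haybittle-Peto rule loses its error control once investigators see results below the boundary.** Continuing below the boundary is what the rule expects, and stopping without an efficacy claim cannot raise the type I error. Inflation would need something more, such as an efficacy claim on a sub-boundary result or an extension chosen in light of the results. The protocol provides for neither.
- **That a known share of the trial would be run under a known trend, at several looks.** The number and timing of looks are left to the DSMB, and there may be none.

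**What to change.** 1. In section 11.2.5.3, replace the two sentences on reporting to the TMG and on joint decision. The DSMB gives the TMG, investigators and sponsor a recommendation only (continue, modify or stop). No comparative efficacy results, coded or not, leave the closed session unless the DSMB recommends stopping or early release.
2. In the same place, state that the investigators and sponsor decide on continuation on the basis of that recommendation.
3. In section 16.2.3.1, limit the written report to the Chief Investigator to the recommendation and open-session content. Without this, the first change leaves a gap.
4. Put the same rule in the DSMB charter, since the charter will supersede the appendix text.

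The cost is a minor protocol amendment, which under section 12.2.2 goes to the LSTM and LSHTM research ethics committees and to the primary ethics committee in each country, plus matching charter text. Sample size, alpha and power do not change.

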### 11.2.5.4 *Safety analysis*

For the safety analysis, data from all subjects from the safety analysis population will be included. All analyses will be descriptive. Data will be summarized by treatment group. The percentage of subjects with at least one AE during the follow-up period will be tabulated with exact 95% CI (two-sided). No multiplicity adjustment will be implemented in analysis. The percentage of subjects with at least one report of unsolicited AE and reported up to 28 days after enrolment will be tabulated with exact 95% CI.

The occurrence of SAEs will be determined on the safety analysis population. The proportion of subjects with an SAE, classified by the MedDRA preferred term level, reported from study start until study conclusion will be tabulated with exact 95% CI. Comparisons between groups will be made using Fisher's Exact Test for each preferred term. Serious adverse events (SAEs) occurring at any point during the trial will be summarised, and relatedness to treatment will be assessed.

## 11.2.6 Missing data

### 11.2.6.1 *Baseline covariates*

Missing baseline covariates in the overall COVID-19 cohort study and nested malaria treatment trial will be imputed using simple imputation methods in the covariate-adjusted analysis based on the covariate distributions, should the missing values for a particular covariate be less than 5%. For a continuous variable, missing values will be imputed from random values from a normal distribution

with mean and SD calculated from the available sample by age group and study site and malaria status. For a categorical variable, missing values will be imputed from random values from a uniform distribution with probabilities  $P_1$ ,  $P_2$ , ..., and  $P_k$  from the sample. The seed for the imputation will be set as a number with 8 digits (e.g. the date of the programming).

If the missing values for a covariate are  $\geq 5\%$ , then they will be imputed using Markov chain Monte Carlo (MCMC) methods.

#### 11.2.6.2 Efficacy outcomes

For the primary analysis, a complete case analysis will be performed, and no imputation for missing efficacy outcome values will be performed.

#### 11.2.7 Multiplicity

Issues of multiplicity will not be considered in this exploratory study.

#### 11.2.8 Pharmacokinetic analysis

Compartmental Population Pharmacokinetic Modelling will be performed using Monolix 2018R2 to establish the pharmacokinetic profile throughout the population and relate to covariates, including patient sex, weight, BMI and malaria/COVID-19 disease status. The pharmacokinetic analysis will also be performed on quantified drug concentrations within saliva samples to establish drug distribution to this compartment and related to predicted lung concentrations using Physiologically Based Pharmacokinetic (PBPK).

Pharmacokinetic-Pharmacodynamic modelling will be similarly performed using compartmental analyses Monolix by linking drug exposure to drug effects quantified through SARS-CoV-2 expression from nasal swabs collected at similar time points to blood samples. Other covariates relating to patient symptoms and recovery status and time will be studied in parallel and separate analyses to investigate any potential PKPD interactions.

## 12 ETHICS AND DISSEMINATION

### 12.1 DECLARATION OF HELSINKI

The trial will be conducted in compliance with the principles of the Declaration of Helsinki (1996) (See section 16.3, Appendix III. Declaration of Helsinki, page 79), the principles of GCP, and in accordance with all applicable regulatory requirements in Kenya and Burkina Faso.

### 12.2 RESEARCH ETHICS AND REGULATORY APPROVAL

#### 12.2.1 Review process

This protocol, the informed consent document, patient information sheets will be reviewed in Kenya, by KEMRI's Scientific and Ethics Review Unit and the Kenyan Pharmacy and Poisons Board and in Burkina Faso, by the National Ethical Committee and the Technical Committee for Clinical Trials (*Comité Technique pour les Essais Cliniques [CTEC]*) of the Ministry of Health. In addition, the protocol will require approval from the Research and Ethics Committee of Liverpool School of Tropical Medicine, Liverpool (LSTM) and the London School of Hygiene and Tropical Medicine (LSHTM).

#### 12.2.2 Protocol amendments

If it is necessary for the protocol to be amended, the protocol amendment will be submitted to the research ethics committees at LSTM and LSHTM (sponsors) and the primary ethics committees in

each country for approval before implementation in that country. Any change to the informed consent form, except for layout, spelling errors and formatting, must also be approved by the sponsor and the primary ethics committee in each country, before the revised form is used.

No change will be made to the approved protocol without the agreement of the sponsor. The Chief Investigators, or a delegated person, will distribute amendments on behalf of the sponsor to each principal investigator, who in turn is responsible for the distribution of these documents to the staff at his/her study site.

### 12.2.3 Sanctioning of the protocol by hospitals

Where this is a requirement of participating hospitals, the approved protocol will subsequently be submitted to the participating hospital's review committees or representatives for subsequent sanctioning of the protocol and procedures by the hospital.

### 12.2.4 Regulatory approval

Regulatory approval for the nested malaria treatment trial will be sought from the national regulators in Kenya and Burkina Faso, respectively. Both artemether-lumefantrine and pyronaridine-artesunate are currently approved under various brand names in each of the countries.

## 12.3 INFORMED CONSENT PROCEDURES

Informed consent and assent will be obtained before participants are enrolled in the screening study (cross-sectional survey, source population) and again when they are eligible for the COVID-19 cohort study. Assent will be obtained for children age 12-19 years in Burkina Faso and 13-17 years (inclusive) in Kenya. See section 16.12, Appendix XII. Participant information sheets and informed consent and assent statements, page 125, for further details.

### 12.3.1 Consent procedures

Written informed consent and assent will be obtained in the local vernacular language (Kenya: Kiswahili, Dholuo, Luhya, Igikuria, Iteso; Burkina Faso: French). The consent process will be initiated at the time of enrolment into the study and will continue throughout the participant's participation. Potential participants will be made aware of the existence of the study by routine staff or by study staff working alongside the routine staff. If the participant meets the study enrolment criteria, the full consent process will follow, with a written consent/assent form provided. The consenting/assenting procedures will be conducted by trained staff who will answer any questions the participants may have. A copy of the informed consent/assent document will be given to the participant for their records unless they state that they do not wish to have a copy.

For illiterate participants, an independent witness will be present during the informed consent process and will sign the consent form as a witness, while the participant will be asked to indicate consent by use of thumbprint. The participant may withdraw consent at any time throughout the course of the study, and this will be made clear in the informed consent/assent process. A copy of the informed consent /assent document will be given to the participant or their caregiver for their records unless they state that they do not wish to have a copy.

All individuals will be informed that there is no requirement to join the study and that standard medical care will remain the same regardless of study enrolment. If the participant or their caregiver chooses not to be enrolled in the study, they will be allowed to continue with routine care provided by the health facility without any consequences to the expected level of care provided.

## 12.4 PROTECTION OF PRIVACY AND CONFIDENTIALITY

### 12.4.1 Privacy

Personal and medical information relating to research participants will be treated as confidential. The risk of disclosure will be minimized by secure storage of documents and use of linked data by replacing personal identifiers with a unique study code to conceal the identity of the participant.

### 12.4.2 Privacy of individual

Individual data such as PCR results for SARS-CoV-2, RDT tests for malaria and anaemia will be reported to the participant at point of care, to relevant study staff and where appropriate will be recorded in the participants' medical record book in addition to CRFs.

### 12.4.3 Confidentiality of data

All information regarding the participants will remain confidential to the extent allowed by law. Unique numerical identifiers will be used for data entry. All screening forms and case report forms will be kept in a secured location with access limited to authorized study staff. Unique numerical identifiers will be used for the computer-based data entry and blood samples. Publications will contain only aggregated data. No identifying information will be included to ensure individual patient anonymization of all data and results made public.

